**Figure 1 figure1:**
[figure not shown]
Participant flow through this waiting list randomized control trial with embedded process evaluation.

### Recruitment

Participants will be recruited by email invitation through the Macmillan Cancer Support database of cancer survivors. An advert will also be placed on the Macmillan Cancer Support Facebook page [53]. Those that express an interest will be sent further participant information by email, with consent provided digitally by check box, following the British Psychological Society ethics guidance for Internet-mediated research [54]. Participants will be informed that the study aims to investigate the impact of health promotion information on lifestyle behaviors, with no specific reference made to physical activity. Participants will be notified that they will be randomized to receive guidelines for a lifestyle behavior or a health promotion pack with Internet-based tools relating to a lifestyle behavior. Recruited participants will be randomized based on simple randomization. Recruitment will continue until 99 participants are randomized to either the control or intervention arm.

### Inclusion Criteria

This study will include cancer survivors regardless of cancer stage, cancer type, or comorbidity. Participants will be aged 18 years or over, who can read English, can provide consent, are computer and Internet literate, and have a working email account.

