### The Move More Pack and its Revision

The UK charity, Macmillan Cancer Support, developed a printed resource in 2011 called the Move More Pack that aimed to effect change in physical activity in cancer survivors. The Move More Pack consisted of a physical activity and cancer booklet and a series of written assignments to support behavior change. No additional assistance or follow-up was provided. The effectiveness of the Move More Pack in effecting change in physical activity in cancer survivors has not yet been investigated.

The principal investigator led the redevelopment of the Move More Pack in 2016 to become a printed resource supported by a series of Internet-based tools. Following discussions with cancer survivors [9,31], a systematic search and critical appraisal of the literature, a review of the original Move More Pack with respect to its underlying theoretical constructs, and an inventory of the behavior change techniques (BCTs) it advocates, recommendations were made.

The theory of planned behavior (TPB) [15,32] and the social cognitive theory (SCT) [33-35] were identified as appropriate theories upon which to base the redevelopment of the Move More Pack. The original Move More Pack was assessed using the constructs of the TPB and the SCT. The BCT taxonomy version 1 (BCTTv1) [36] identified the active ingredients that aimed to effect change and those that might be missing from the original design. Following an iterative process, a group of six subject experts including the principal investigator, in partnership with Macmillan Cancer Support’s information development team, refined the structure, content, and BCTs included within the revised Move More Pack. Macmillan Cancer Support’s information development team wrote the final copy of the revised Move More Pack. [name], Macmillan Cancer Support’s chief medical editor, approved the final version. The revised Move More Pack received the National Health Service England (NHS England) Information Standard [37]. A PDF of the revised Move More Pack is included as Multimedia Appendix 1.

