### Exclusion Criteria

There are greater risks from being inactive than taking part in physical activity. The revised Move More Pack does not prescribe exercise in any way, and the relevant safety information is sent in the post to participants at the start of the study. The safety information is taken from the Macmillan Cancer Support Web pages [55] and has received the NHS England Information Standard [37]. However, those participants considered at high risk of injury are excluded from this study. On the basis of guidance on exercise and cancer survivorship from the American College of Sports Medicine [7,56], reviewed and approved by subject experts from Macmillan Cancer Support’s physical activity team, the following screening questions will be asked of participants, with an answer of yes to any question resulting in exclusion from the study:

Are you less than 8 weeks postsurgery?Are you experiencing extreme fatigue, anemia, or severe balance and coordination problems?Do you have cancer in your bones or bone thinning?Do you have a heart or lung condition (excluding lung cancer)?Do you feel pain in your chest at rest, during your daily activities, or when becoming active?Do you have persistent pain in your muscles, bones, or joints?Do you have swelling or inflammation in the abdomen, groin, or lower extremity?Has your doctor ever said that you should only do medically supervised physical activity?Are you pregnant?

Excluded participants will be informed that they will need medical approval before becoming more physically active and, therefore, are not eligible for this study. They will be thanked for their time and given the details of how to order the free resources offered to participants in this study, for use after receiving permission from their general practitioners or cancer care teams, should they decide to become more active.

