### Procedures and Assessment Tools

#### Effectiveness

Physical activity will be assessed using the GLTEQ, a reliable and validated tool [43] used previously with cancer survivors [57]. The cancer specific 7-item Functional Assessment of Cancer Therapy Questionnaire (FACT-G7), also a reliable and validated tool, will be used to assess HRQOL [58].

The GLTEQ and the FACT-G7 will be administered electronically at baseline in the intervention and control arms of the study. Participants will be asked to complete the GLTEQ twice:

To consider their levels of activity in a standard week before their cancer diagnosis, to allow for the tailoring of the e-newsletters, and to provide a context for the use of the revised Move More Pack.To consider their levels of activity in a standard week after diagnosis, as a baseline assessment of physical activity.

Self-efficacy will be assessed using the following single-item assessment tool: “On a scale of 1 to 10 (1=not at all confident and 10=very confident), how confident are you that you will be physically active in situations such as the following: feeling tired, bad mood, not having the time, on vacation, bad weather?” A similar measure has been used previously with cancer survivors [59]. A single-item assessment tool is selected for its practical application to a real-world setting, and furthermore, single-item assessment tools can perform just as well as multi-item assessment tools [60].

Additional participant information will be collected on date of birth, gender, primary cancer site (type), time since diagnosis, treatment received, time since completion of treatment, response to treatment, and ethnic group. The structure of these questions is that used by NHS England [13]. These questionnaires and participant data will be collected using software from Qualtrics, USA.

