### Ethical Considerations

The information included in the revised Move More Pack is certified by the NHS England Information Standard [37]. The NHS England Information Standard ensures that publically available information has undergone rigorous assessment, is evidence-based, of high quality, clear, accurate, and appropriate for its intended audience. The revised Move More Pack does not prescribe exercise. The relevant safety information is sent to participants in the first postal communication. Criteria for cessation of physical activity is provided, for example, sudden onset of dizziness, chest pains, a racing heartbeat, breathing problems, nausea, unusual back or bone pain, muscle weakness or a persistent headache, advising participants to contact their doctors for these or other symptoms. Appropriate screening is in place within the study procedures to identify participants needing medical permission before increasing their physical activity, with these participants being excluded from this study. A log of participant issues will be maintained throughout the study, and participants will be offered a phone debriefing session at the end of the study.

Participants in the control arm will not be restricted with regard to being physically active. The participants in the control arm will be asked as part of the questionnaire instructed at the 12-week follow-up time point if they have used the revised Move More Pack within the previous 12 weeks, with their data omitted from the study if they have. This study received ethical approval from the University of Surrey Research Ethics Committee on March 15, 2017, reference UEC/2017/023/FHMS.

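### As listed, entry neither screens for nor records earlier use of the freely orderable revised pack, so prior users can enter both arms and may weaken the 12-week contrast

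*Protocol article*

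**What the plan says.** All references are to the protocol article.

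- **Inclusion Criteria:** "This study will include cancer survivors regardless of cancer stage, cancer type, or comorbidity". The remaining requirements are these: "Participants will be aged 18 years or over, who can read English, can provide consent, are computer and Internet literate, and have a working email". Neither sentence mentions the pack.
- **Exclusion Criteria:** the stated purpose is safety ("However, those participants considered at high risk of injury are excluded from this study"). All nine screening questions are medical.
- **Effectiveness (under Procedures and Assessment Tools):** besides the activity, quality-of-life and self-efficacy questionnaires, the section says: "Additional participant information will be collected on date of birth, gender, primary cancer site (type), time since diagnosis, treatment received, time since completion of treatment". Two further items, on ethnicity and how the disease responded, complete the list. Earlier receipt or use of the pack is not in it.
- **Recruitment:** "Participants will be recruited by email invitation through the Macmillan Cancer Support database of cancer survivors", together with an advert on the same charity's Facebook page.
- **Availability outside the trial:** people who fail screening are "given the details of how to order the free resources offered to participants in this study".
- **Timing:** "The principal investigator led the redevelopment of the Move More Pack in 2016" (The Move More Pack and its Revision). Recruitment began in March 2017 (Results).
- **The only exposure check (Ethical Considerations):** at the 12-week follow-up, controls are asked "if they have used the revised Move More Pack within the previous 12 weeks". Those who say yes have their data left out.

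**The concern.** The week-12 question shows that the authors regard use of the pack outside the trial as contaminating the control arm. The same reasoning applies to use before entry, and the article's lists do not cover it. A control participant who used the revised pack before enrolment may already carry its effect. An intervention participant with the same history is sent something already used. Neither adds much to the difference between arms.

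The week-12 check does not close this gap. It comes after randomisation, goes to one arm, and looks back only over the trial period. A control who used the pack before entry and then stopped can truthfully answer no. A control who is still using it is removed, while an intervention participant with the same history stays.

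At stake is the reading of the primary result. If prior use is not recorded, a small or null difference could mean that the pack does little, or that some participants had already had it, and no later analysis could separate the two.

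**Working it through.** **Inputs from the article.** 23% active to guideline level; an increase of 18%, read as percentage points, which gives 41%; 82 per arm; one-tailed 5%; 80% power (all Sample size). Two-proportion z test on the proportion classified as active (Data Analysis). The calculation treats the two definitions of active as the same.

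**Assumed inputs, not in the article.** The share *s* of entrants who have already used the revised pack, taken as 5%, 10% and 20%, equal in both arms; and no further gain from the trial pack in those people.

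**Step 1: reproduce the plan's figure.** With pooled null variance and no continuity correction,

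n = [z₀.₉₅ √(2p̄(1−p̄)) + z₀.₈₀ √(p₁(1−p₁) + p₂(1−p₂))]² / (p₂−p₁)²

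with p₁ = 0.23, p₂ = 0.41, p̄ = 0.32:

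n = [1.645 × √0.4352 + 0.842 × √0.4190]² / 0.18² = 82.

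This matches the article, and power at 82 per arm is 0.800.

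**Step 2: dilute the difference.** If prior users show no between-arm difference, the expected difference is 18 × (1−s) points. Where prior users sit affects the variance, so two cases are shown:

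- Case A, already at 41% in both arms: control = 0.23 + 0.18s, intervention = 0.41.
- Case B, at 23% in both arms: control = 0.23, intervention = 0.23 + 0.18(1−s).

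**Step 3: power at 82 per arm.** Power = Φ{[(p₂−p₁)√82 − 1.645 √(2p̄(1−p̄))] / √(p₁(1−p₁) + p₂(1−p₂))}.

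| Assumed share s | Difference (points) | Power, case A | Power, case B | n per arm for 80% (A / B) |
|---|---|---|---|---|
| 0% | 18.0 | 0.800 | 0.800 | 82 / 82 |
| 5% | 17.1 | 0.760 | 0.765 | 92 / 91 |
| 10% | 16.2 | 0.716 | 0.728 | 103 / 100 |
| 20% | 14.4 | 0.621 | 0.644 | 133 / 125 |

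**Step 4: partial benefit.** If prior users still gain a fraction r of the effect, the difference is 18 × [1 − s(1−r)]. A 10% share gaining half the effect gives 18 × (1 − 0.10 × 0.5) = 17.1 points. That is the 5% row, with power about 76%.

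**Step 5: the control-only omission.** Take case A with s = 10%. The control proportion is 0.23 + 0.018 = 24.8%, and the difference from 41% is 16.2 points. If every prior user is still using the pack, and so is dropped from control only, control returns to 23% and the difference becomes 18.0 points. The intervention arm still contains the same kind of people. The observed difference moves because the groups compared are no longer those randomised, which also sits badly with the intention-to-treat statement in Data Analysis.

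**The case against.** **The article does not show that prior users enter.** A reader might infer that already-exposed people are in both arms and are diluting the effect. The text does not support that. It gives the redevelopment year but no public release date, so the period before March 2017 may be short. Being on the charity's database does not mean having had the pack. This objection stands: the text supports only that prior users can enter.

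**There is no bias between arms at entry.** A reader might infer that the primary contrast is biased. Randomisation balances prior users in expectation, so the contrast is valid for the people enrolled, and taking all comers suits a trial with real-world aims. This also stands. The loss is relative to pack-naive survivors, and it costs power.

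**The 2011 original is a different intervention.** The article describes a restructured pack with added components and says that the original's effectiveness had not been studied. Use of the original cannot be counted as exposure.

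**Zero further benefit is extreme.** Trial participants also receive e-newsletters through month 3 and directions to the Internet-based tools, and an earlier recipient may have used only part of this. The table is therefore the unfavourable end for each assumed share.

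**Partly handled already.** The week-12 question does catch controls still using the pack. It misses those who stopped, and it treats the arms unequally.

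**An article condenses.** The full questionnaire is not shown and could hold such an item, so the point is limited to what is listed. But the article sets out its eligibility criteria and screening questions in detail, and these are protocol matters, not details left to an analysis plan.

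**Conclusion.** The point holds in a limited form. As listed, eligibility and baseline data leave earlier use of the revised pack unscreened and unrecorded, in a setting where such use is plausible, and the one exposure check does not cover it.

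The consequence is possible attenuation of the 12-week effect relative to pack-naive survivors and a loss of power, both of unknown size. On assumed shares of 5%, 10% and 20%, equal across arms and with no further gain, power at 82 evaluable per arm drops from 80% to about 76%, 72-73% and 62-64%. Any remaining benefit makes the loss smaller. These figures illustrate sensitivity and do not estimate what will happen. They take 82 as the analysed number. If all 99 per arm were analysed, undiluted power would be about 86%, and the losses would start from there.

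**What to change.** Add one item to the web screener, answered by everyone before randomisation, asking which of several of the charity's resources they have received or used. Listing both versions of the pack among unrelated resources keeps the physical-activity focus concealed, as the Recruitment section intends.

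- Exclude prior users of the revised pack before randomisation. Exclusion at that stage cannot unbalance the arms.
- For participants already enrolled, where exclusion is no longer possible, ask both arms about use before enrolment. Record it as a baseline variable and prespecify a sensitivity analysis that uses it in both arms.
- Record use of the original pack as a descriptive baseline variable only.

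With prior users screened out, the sample-size inputs stand unchanged and the week-12 question deals only with access gained after entry.

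The cost is one questionnaire item, one eligibility line and a few respondents who become ineligible. Because recruitment began in March 2017 under an existing ethics approval, a minor amendment is needed if enrolment is still open, and people enrolled before and after it will have met different criteria, which should be reported.

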### Exclusion Criteria

There are greater risks from being inactive than taking part in physical activity. The revised Move More Pack does not prescribe exercise in any way, and the relevant safety information is sent in the post to participants at the start of the study. The safety information is taken from the Macmillan Cancer Support Web pages [55] and has received the NHS England Information Standard [37]. However, those participants considered at high risk of injury are excluded from this study. On the basis of guidance on exercise and cancer survivorship from the American College of Sports Medicine [7,56], reviewed and approved by subject experts from Macmillan Cancer Support’s physical activity team, the following screening questions will be asked of participants, with an answer of yes to any question resulting in exclusion from the study:

Are you less than 8 weeks postsurgery?Are you experiencing extreme fatigue, anemia, or severe balance and coordination problems?Do you have cancer in your bones or bone thinning?Do you have a heart or lung condition (excluding lung cancer)?Do you feel pain in your chest at rest, during your daily activities, or when becoming active?Do you have persistent pain in your muscles, bones, or joints?Do you have swelling or inflammation in the abdomen, groin, or lower extremity?Has your doctor ever said that you should only do medically supervised physical activity?Are you pregnant?

Excluded participants will be informed that they will need medical approval before becoming more physically active and, therefore, are not eligible for this study. They will be thanked for their time and given the details of how to order the free resources offered to participants in this study, for use after receiving permission from their general practitioners or cancer care teams, should they decide to become more active.

### Procedures and Assessment Tools

#### Effectiveness

Physical activity will be assessed using the GLTEQ, a reliable and validated tool [43] used previously with cancer survivors [57]. The cancer specific 7-item Functional Assessment of Cancer Therapy Questionnaire (FACT-G7), also a reliable and validated tool, will be used to assess HRQOL [58].

The GLTEQ and the FACT-G7 will be administered electronically at baseline in the intervention and control arms of the study. Participants will be asked to complete the GLTEQ twice:

To consider their levels of activity in a standard week before their cancer diagnosis, to allow for the tailoring of the e-newsletters, and to provide a context for the use of the revised Move More Pack.To consider their levels of activity in a standard week after diagnosis, as a baseline assessment of physical activity.

Self-efficacy will be assessed using the following single-item assessment tool: “On a scale of 1 to 10 (1=not at all confident and 10=very confident), how confident are you that you will be physically active in situations such as the following: feeling tired, bad mood, not having the time, on vacation, bad weather?” A similar measure has been used previously with cancer survivors [59]. A single-item assessment tool is selected for its practical application to a real-world setting, and furthermore, single-item assessment tools can perform just as well as multi-item assessment tools [60].

Additional participant information will be collected on date of birth, gender, primary cancer site (type), time since diagnosis, treatment received, time since completion of treatment, response to treatment, and ethnic group. The structure of these questions is that used by NHS England [13]. These questionnaires and participant data will be collected using software from Qualtrics, USA.

#### 12-Week Follow-Up

The effectiveness of the revised Move More Pack at effecting change in physical activity, self-efficacy, and HRQOL in the intervention arm will be evaluated after 12 weeks using the assessment tools used at baseline. The control arm will also be assessed at this 12-week time point. Participants will not have access to their previous scores.

At the 12-week time point, participants in the control arm will be mailed the revised Move More Pack, directed to the Internet-based tools, and will receive the e-newsletters as outlined. The control arm will be followed up a further 12 weeks later, at 24 weeks, to evaluate change in physical activity, self-efficacy, and HRQOL. Participants in the intervention arm will continue to have access to the Internet-based tools, although they will no longer receive e-newsletters after the 12-week time point.

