**Methods:**

This study is a two-arm waiting list randomized control trial with embedded process evaluation. A sample of 99 participants per arm will be recruited by invitation through an email database of cancer survivors held by UK charity Macmillan Cancer Support and an advert placed on the Macmillan Cancer Support Facebook page. Each participant is randomized to receive brief physical activity information and the UK guidelines for physical activity, or brief physical activity information and the revised Move More Pack with supporting Internet-based tools. The intervention and control arm will be followed up at 12 weeks to identify changes in self-reported physical activity, self-efficacy, and HRQOL based on Web-based questionnaires. The control arm will receive the revised Move More Pack at 12 weeks with follow-up at 24 weeks. The intervention arm is followed up at 24 weeks to determine maintenance of reported changes. Subgroup analyses will be completed based on participants’ prediagnosis level of physical activity and baseline self-efficacy as possible predictors of positive changes. Use of each component of the revised Move More Pack will be assessed using a 4-point Likert scale. Semistructured phone interviews will evaluate the use and perceived usefulness of the revised Move More Pack.

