#### Maintenance

The maintenance of reported changes in physical activity, self-efficacy, and HRQOL for participants in the intervention arm will be evaluated after 24 weeks with the same assessment tools. Participants will not have access to their previous scores.

Participants will be informed that they can withdraw from the study at any time by contacting the principal investigator. In such cases, the reason for withdrawal from the study will be ascertained and recorded. Nonresponders to the questionnaire will be followed up by email to record their reasons for dropping out of the study.

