The major limitation of this study is the use of self-reported measures to assess and evaluate participants’ physical activity, self-efficacy, and HRQOL. The measures selected are validated and reliable. The GLTEQ has been used in previous research with cancer survivors [57], and the FACT-G7 is specifically designed for cancer survivors [58]. The self-reported measures have been selected for their ease of implementation in a real-world setting. Whereas the use of an objective measure of physical activity may be preferable, this would introduce an additional behavior change technique. Furthermore, as the revised Move More Pack aims to enable cancer survivors to monitor their physical activity by directing them to use a pedometer, introduction of an objective measure may influence the effectiveness of this component of the revised Move More Pack.

Some studies of cancer survivors have reported high levels of dropout [69]. Therefore, an additional 20% will be recruited to this study. Furthermore, a combination of strategies will be employed to encourage participants to complete the relevant questionnaires at the data collection points, including email and text reminders.

It is possible that the exclusion criteria for this study may result in a selection bias; however, the safety of the participants will not be compromised. In addition, as participants are recruited through the channels of Macmillan Cancer Support, they may not be representative of the population of cancer survivors in the United Kingdom. The profile of the included participants will be reported and any selection bias identified.

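### The control arm's 12-week assessment and the release of the pack share one time point, and release does not depend on the questionnaire being returned, so late control responders may already hold the pack

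*Protocol article*

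**What the plan says.** The 12-Week Follow-Up section of the protocol article puts two control-arm events at one time point.

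- **Assessment:** "The control arm will also be assessed at this 12-week time point".
- **Release:** "At the 12-week time point, participants in the control arm will be mailed the revised Move More Pack, directed to the Internet-based tools". The e-newsletters also start for this arm.

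The Abstract (Methods) gives the same release time: "The control arm will receive the revised Move More Pack at 12 weeks with follow-up at 24 weeks". The 12-Week Follow-Up section then sets the next control assessment a further 12 weeks on and equates that with week 24.

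Three other places bear on the point.

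- **Discussion:** the plan will "encourage participants to complete the relevant questionnaires at the data collection points, including email and text reminders". It does not say how long the reminders run.
- **Maintenance:** "Nonresponders to the questionnaire will be followed up by email to record their reasons for dropping out of the study".
- **Ethical Considerations:** the 12-week questionnaire asks controls "if they have used the revised Move More Pack within the previous 12 weeks, with their data omitted from the study if they have".

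Data Analysis states that the quantitative data are analysed by intention to treat, and that the proportions classified as active are compared between arms with a two-proportion z test.

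**The concern.** The outcome is a web questionnaire that participants complete themselves, and the plan itself foresees reminders. Some control answers may therefore arrive after week 12. Because release follows the time point and not the returned questionnaire, such a participant may hold the pack and the links before answering. The two possible consequences differ:

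- **Used the pack and says so.** The data are omitted. Only controls can be removed in this way, the removal follows randomisation, and the trial's own mailing caused it. This does not fit an intention-to-treat analysis. The item looks back 12 weeks, so it also cannot separate a control who obtained the pack independently during the control period from one who opened the copy the trial sent.
- **Received the pack but does not report use.** The data stay in the control arm as if unexposed. Any effect of the material pulls the arms together.

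Controls are offered the pack from week 12, so the 12-week contrast is the only randomised comparison with a control arm not yet offered it. That contrast carries the primary aim.

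**Working it through.** **1. Reproduce the plan's figure.** Inputs from Sample size: 23% active, an increase of 18 points (to 41%), one-tailed alpha 5%, power 80%.

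n per arm = [z(0.95)·√(2p̄(1−p̄)) + z(0.80)·√(p₁(1−p₁) + p₂(1−p₂))]² / (p₂−p₁)², with p̄ = 0.32

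- 1.645 × √0.4352 = 1.085
- 0.842 × √(0.1771 + 0.2419) = 0.545
- (1.085 + 0.545)² / 0.0324 ≈ 82

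This matches the stated 82 per arm, and power at 82 per arm is 80.0%. No stated figure is wrong because of the timing issue.

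**2. Late controls who are kept.** Let f be the share of control responders who answer after receiving the pack, and r the share of the 18-point effect they show by then. Neither is in the documents; both are assumed. The control rate becomes 0.23 + 0.18·f·r, and power is recalculated at 82 per arm with the same test.

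| f | r | Control rate | Difference (points) | Power |
|---|---|---|---|---|
| 0 | – | 23.0% | 18.0 | 80.0% |
| 5% | 0.25 | 23.2% | 17.8 | 79.0% |
| 5% | 0.5 | 23.45% | 17.55 | 78.0% |
| 10% | 0.25 | 23.45% | 17.55 | 78.0% |
| 10% | 0.5 | 23.9% | 17.1 | 76.0% |
| 20% | 0.5 | 24.8% | 16.2 | 71.6% |

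For example, f = 10% and r = 0.5 gives 0.23 + 0.18 × 0.1 × 0.5 = 0.239.

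**3. Late controls who are omitted.** The control arm shrinks to 82(1−f), the intervention arm stays at 82, and the rates stay at 23% and 41%.

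| f omitted | Controls left | Power |
|---|---|---|
| 5% | 77.9 | 79.0% |
| 10% | 73.8 | 78.0% |
| 20% | 65.6 | 75.5% |

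These figures cover lost numbers only. Any selection bias from removing controls according to what they did after randomisation comes on top and cannot be sized from the documents.

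**4. The two losses do not add for the same person.** A late control who reports use is omitted and cannot also dilute the difference. Steps 2 and 3 are alternatives for any one participant.

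**The case against.** The strongest reply is that the article never says the pack goes out while questionnaires are outstanding. It describes the assessment before the mailing and gives no interval between them. The reminders have no stated duration and could all precede the mailing. The email to nonresponders records reasons for dropping out, which suggests that nonresponse is treated as dropout and not as an outcome still to be collected. The participant-flow figure is not available here, and mailing triggers and response windows are details an article often leaves to the full protocol.

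Much of this stands. A reader might infer three stronger things that the documents do not support:

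- **That late control answers will in fact follow receipt of the pack, or that many will be late.** Nothing states the order of events within week 12 or a late-response rate. Exposure before answering is something the procedure permits, not something it makes certain.
- **That all exposed controls are counted as unexposed.** Those who report use are omitted. Only those who hold the pack without reporting use are kept, and they are probably the least affected by it.
- **That the power loss is large.** Half of a 12-week effect soon after a posted pack arrives is a generous assumption, and a high late share has no basis in the text.

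The reply does not remove the point. The article goes beyond leaving a detail out: it gives a release time, repeats it in the Abstract, and ties the next assessment to a fixed week 24. If release waited for each return, a further 12 weeks would not end at week 24 for a late responder. Followed as written, the rule allows exposure before a late answer.

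**Conclusion.** The point holds as a weakness in a stated rule. Assessment and release coincide, release is not conditional on the questionnaire, and reminders are planned. A late control responder may therefore be exposed before answering and then be either omitted, contrary to intention to treat, or kept as unexposed.

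The size cannot be fixed from the documents. With an assumed 5% to 10% of controls late and showing a quarter to half of the effect, power falls from 80% to about 76% to 79%, a loss of roughly 1 to 4 points. Omitting 10% instead leaves about 78%. Dilution biases towards no difference; the direction of bias from omission depends on who is removed and is unknown. This is a cheap improvement of modest, unquantified benefit. It does not invalidate the design or the sample size.

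**What to change.** **12-Week Follow-Up.** Replace release at the 12-week time point with a rule such as: the pack, links and e-newsletters are released to a control participant only after that participant's 12-week questionnaire has been submitted, or when a stated response window closes, whichever comes first. Use the same window in both arms. Count the control arm's further 12 weeks from the release date, and bring the Abstract into line.

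**Ethical Considerations.** Limit the pack-use question to the period before release, so that it records only use the trial did not itself cause.

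**Cost.** A wording change and a mailing list triggered by submission. Late responders receive the pack, and have their final follow-up, later by up to the length of the window.
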